### Secondary endpoints

6.2

1.Changes in nutritional management and severity of dysphagia will be assessed by:Dysphagia status as measured by DOSS at baseline, day 2 (approx. 24–60 hours), 7 ± 1 days and at 14 ± 1 days (or hospital discharge if earlier) after completion of the final PES treatment (to assess changes in functional severity of dysphagia over time),Time (days) from randomization to removal of feeding tube,Time (days) to first oral intake (if applicable. Oral intake is minimally defined as movement from for example FOIS 3 (Tube dependent with consistent intake of liquid or food) to FOIS 4 (Total oral diet of a single consistency) or from DOSS 2 (Moderately severe dysphagia) to DOSS 3 (Moderate dysphagia),Total days of enteral feeding,FOIS scale at baseline, day 2 (approx. 24–60 hours), 7 ± 1 days and at 14 ± 1 days (or hospital discharge if earlier) after completion of the final PES treatment.General health outcomes will be assessed by:Time (days) from extubation to ICU discharge,ICU LOS (Length of stay in ICU),Hospital LOS (Length of stay in hospital)Number of patients with re-intubation during hospital stayMortality.

### Other endpoints and supplementary data collected

6.3

Additional data for exploratory analysis will be collected in relation to dysphagia severity and general patient outcomes. For changes in severity of dysphagia between FEES assessments, the IFRC will evaluate secretion severity (Murray Secretion Severity Rating Scale (SSS)), bolus residue (Yale Pharyngeal Residue Severity Rating Scale (YRS)) and global dysphagia severity (Global Dysphagia severity Score (GDS). Further, swallowing safety and efficiency will be analyzed using the worst PAS score for each bolus consistency for each patient as determined by a FEES assessment on day 2 (approx. 24–60 hours) after completion of final PES treatment, converted to a dichotomized ordinal response of non-aspirator (PAS 1–5) or aspirator (PAS 6–8) (performed to address presence of aspiration, a key medical problem). General patient health outcome data collected and to be analyzed include time from extubation to hospital discharge (days), days on antimicrobials post-extubation (while in ICU), hospital discharge destination (home, home + care, nursing home, other hospital, rehabilitation center), ICU readmission rate during hospital stay, number of and reason for tracheostomies per group after PES treatment during hospital stay and total number of chest X-rays during hospital stay after ICU discharge for suspected pneumonia. Phagenyx treatment parameters (catheter insertion-related, ease of use, threshold, tolerance and stimulation levels) and nursing workload (TISS-28) data will also be collected.

## Study intervention and comparator

7

For the study intervention (active PES) and sham (comparator), a commercial device (Phagenyx, Phagenesis Ltd, Manchester, UK), which comprises a nasogastric feeding catheter housing stimulation ring-electrodes, and a computerized base station that delivers stimulation in the range 1 to 50 mA at 5 Hz will be used. All eligible patients will undergo PES catheter placement. Appropriate adjustment and placement of the PES catheter in each patient is ensured using catheter markings, aspirate test or X-ray, and fixation of the catheter using a securing clamp. Catheter ease of use will be documented in the eCRF. PES treatment (active) and sham (comparator) will be delivered for 10 minutes per day (as per the device's programming and CE) for 3 consecutive days^[33,34]^ after randomization and performed by a health care professional (nurse, therapist, or physician) unblinded to treatment assignment (PES treater). Sham treatment will be performed using the same device without delivering any energy. To deliver (active) PES, the current intensity (mA) at which PES-treatment will be delivered is individually adjusted and optimized at the start of each treatment session by the PES treater in response to patient responses. This treatment optimization procedure involves increasing the current intensity incrementally from 1 mA to detect the perceptual threshold (PT – patient first aware of stimulation) and then to a maximum tolerated threshold (MTT – patient no longer wants current increased further) intensity levels three times each respectively. Thereafter, the optimal treatment intensity is automatically calculated by the base station using the average values of the three trials according to the formula PT + 0.75 × (MTT − PT).^[26,35]^

To deliver sham PES, the optimization procedure is imitated exactly as in (active) PES to mitigate any bias or effect of time spent interacting with the patient during (active) PES, however, no current is applied. Treatment parameters will be documented in the eCRF.

## Randomization

8

Patients will be randomly allocated to PES treatment or sham (comparator) according to a permutated block randomization stratified by site and reason for ICU admission (neurological vs non-neurological according to APACHE IV diagnostic criteria) using a random mixture of blocks of size 2 and 4. The randomization ratio will be 1:1. The PES treater(s) at site shall not be blinded to the patient's randomization assignment in order to be able to deliver PES treatment or sham (comparator). Randomization assignment will be via the web-based study EDC with access restricted to authorized PES treaters. The randomization page of the EDC will only become available once the patient is confirmed to have met all of the inclusion/exclusion criteria and the treatment catheter is successfully placed and tolerated.

## Procedures for emergency unblinding

9

In the event of a medical emergency which requires identification of an individual patient's randomization and (PES or sham) treatment information, investigators will be able to access this information via the PES treater(s). Reasons for unblinding will be documented in the patient's medical records.

## Study assessments

10

### Screening and baseline assessments

10.1

Informed consent will be obtained at the screening visit, by the local principal investigator (or designee) from the patient or their legal representative according to respective local/national guidelines using approved consent forms (study flowchart Fig. 1). A SPIRIT figure is provided (Fig. 2).

**Figure 2 F2:**
[figure not shown]
SPIRIT Figure.

In addition to the assessments detailed below, a medical history, demographic data and the patient's current medical status will be recorded at the baseline visit. Medical history and demographic data will be obtained from the patient's medical record. Other information captured will include: functional severity data (e.g., APACHE II, SAPS II), BMI, RASS, nursing workload (TISS-28), standard of care dysphagia care and feeding / nutrition being provided to the patient, ET tube and tracheostomy status. Information obtained from these assessments will be recorded in the eCRF.

### Fiberoptic endoscopic evaluation of swallowing (FEES)

10.2

FEES is recognized, validated, and routinely used in many hospitals across Europe for instrumental dysphagia assessment. It is considered a gold standard technique for airway- and swallow-safety^[19–22]^ assessment and is the recommended methodology in current guidelines.^[20,36]^ Complications such as discomfort, gagging, vomiting, vaso-vagal syncope, anterior or posterior epistaxis or rare complications such as laryngospasm are expected to occur in < 1% of examinations.^[23]^ In this study, FEES will be performed via nasal induction of an endoscope into the pharynx with visualization of the larynx (details are given elsewhere ^[1]^). FEES assessments will be conducted at screening and on day 2 (approx. 24–60 hours) after completion of the final PES treatment. The FEES assessment will capture:

1 × 30 second video prior to any boli stimuli to assess secretions severity.4 × 10 ml swallow trials with thin liquid (water, International Dysphagia Diet Standardisation Initiative (IDDSI ^[37]^) level 0) stimuli.2 × 10 ml swallow trials with semi-solid (puree, IDDSI level 4) stimuli.2 × non-obligatory soft and bite-sized swallow trials with solid (white bread without the crust approximately 1.5 cm × 1.5 cm × 0.5 cm, IDDSI level 6) stimuli presented only to patients in whom no residues are observed on thin liquid and puree swallow trials.

Data will be entered in the eCRF. Coded video records will also be provided to the IFRC for further analysis and validation of local PAS scores for the thin liquid stimuli (for (re)training purposes only). IFRC members will score videos blinded to the site and other member's scores to allow unbiased scoring. FEES results will not be scored in duplicate, PAS ratings by the local site investigator will be used for all primary endpoint analyses and clinical decision-making.

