### Design

3.1

Prospective, multi-center, 1:1 randomized, sham-controlled, patient-masked, outcome assessor-blinded study designed to assess the effects of PES for the treatment of oropharyngeal dysphagia after invasive mechanical ventilation (of any length of time; by means of naso- or oro-tracheal tube) in critically ill intensive care unit (ICU) patients (active study protocol version 1.0, dated Nov 8, 2018). A study flowchart is provided (Fig. 1). Patient randomization will occur after dysphagia severity is classified as ‘aspiration’ (PAS score ≥ 6) on FEES assessment, and the Phagenyx Catheter is successfully placed. Randomization will be on a 1:1 basis at each site stratified for neurological vs non-neurological reason for admission (APACHE IV diagnostic group). All randomized patients will receive either PES treatment or sham (comparator) by a health care professional who is unblinded to the treatment assignment (PES treater). Sham treatment will be performed using the same device without delivering energy. Administration of all protocol-specific assessments, other than PES or sham, will be conducted by study personnel who are blinded to the treatment assignment, including therapists delivering standard dysphagia care (other forms of electrical stimulation treatment for dysphagia are not permitted in this study). FEES assessments of swallowing safety and decisions on patient treatment will be made by the local clinical team responsible for the patient's care. Study data will be collected using an electronic Case Report Form (eCRF) (SYNCRONY, Syntactx Technologies LLC, NY).

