**Figure 1 F1:**
[figure not shown]
Study flowchart.

An Independent FEES Review Committee (IFRC), external to the study sites, will be established for analysis of all study-related FEES assessment parameters and to confirm/validate the PAS scoring of the local clinical FEES assessor(s). FEES results will not be scored in duplicate but discrepancies in ratings between the local team and IFRC, or concerns about the quality of submitted records will be reviewed and discussed with the local team for (re-)training purposes only. All FEES records will be coded so that records are only identified by site number, bolus number, patient number, and study visit (i.e., screening or follow-up). The IFRC will be blinded to the treatment assignment as well as the actual treatment received.

Six or more investigational academic hospital sites across Europe are anticipated to participate in this study. Factors considered for site qualification of ICUs include, but are not limited to: potential number of suitable patients, availability, and experience of conducting FEES. The enrolment period is expected to be approximately 48 months from the time of first patient recruitment to the final study visit. Each patient's participation will last for up to 90 days with assessments at the following intervals: screening, baseline, day 2 (approx. 24–60 hours), 7 ± 1 days, 14 ± 1 days or hospital discharge (whichever is first) after completion of the final PES treatment. 30-day and 90-day mortality data will also be collected from the patients (electronic health record) medical notes - this will not require an additional visit but a phone call may be conducted depending on the patient's status. Dysphagic patients enrolled into the study will continue to receive nutrition as deemed appropriate by the ICU team. Patients with a nasogastric feeding tube in place at the time of screening/enrolment will have their nasogastric tube replaced with the Phagenyx Catheter since the Phagenyx Catheter may also be used to deliver nutrition to the patient as required for up to 30 days after placement.

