### Penetration aspiration scale score (incl. definitions):

11.1

The PAS is a validated 8-point ordinal scale that quantifies penetration and aspiration events observed during instrumental swallow assessment.^[38]^ The scale ranges from 1 (normal swallow: material does not enter airway) to 8 (severe aspiration: material enters the airway, passes below the vocal folds & no effort is made to eject). Swallowing severity will be assessed using the PAS observed during FEES at screening and on day 2 (approx. 24–60 hours) after completion of the final PES treatment. The worst PAS score for each thin liquid bolus will be recorded in the eCRF. IFRC PAS scores will be entered in a separate portion of the eCRF.

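### The primary PAS is the local rating, which patients who sense or miss the current could influence; the committee's blinded PAS, already collected, is kept for training only

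*Protocol article*

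**What the plan says.** All references are to the protocol article.

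- **Blinding claimed.** Section 3.1 describes a "Prospective, multi-center, 1:1 randomized, sham-controlled, patient-masked, outcome assessor-blinded study". It also says that assessments other than PES or sham are done by staff who do not know the arm. Section 8 restricts access to the assignment to the PES treaters. Section 18 says that blinding of the sponsor and of the assessing site staff is ensured.
- **Active and sham treatment.** Section 7 defines "the perceptual threshold (PT – patient first aware of stimulation") and the maximum tolerated threshold (MTT), and sets the treatment current "according to the formula PT + 0.75 × (MTT − PT"). For sham, the threshold procedure is imitated, but "Sham treatment will be performed using the same device without delivering any energy".
- **Whose PAS counts.** Section 3.1 gives the FEES to the local team that cares for the patient. Section 10.2 fixes that "PAS ratings by the local site investigator will be used for all primary endpoint analyses and clinical decision-making".
- **The committee's PAS.** Section 3.1 describes an external review committee (IFRC) that knows neither the allocation nor the treatment given. Section 10.2 limits its check of local PAS to (re)training. Section 11.1 adds that "IFRC PAS scores will be entered in a separate portion of the eCRF".
- **Coding of videos.** Section 3.1: "All FEES records will be coded so that records are only identified by site number, bolus number, patient number, and study visit". Section 10.2: "IFRC members will score videos blinded to the site".

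**The concern.** The local assessor's blinding depends partly on the patient's. By the protocol's own definition of PT, an active patient feels the stimulation in each of three sessions whenever MTT exceeds PT. A sham patient is taken through a threshold search with nothing to feel. Patients are awake (RASS −1 to +2), and severe cognitive impairment that prevents compliance is an exclusion, so many could notice and comment.

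The person who hears the comment may be the person who rates the day-2 PAS. That rating is the first level of the Finkelstein-Schoenfeld hierarchy, and section 18 concedes that the scales leave some room for interpretation. A rating shift in one arm would enter the primary result directly, and a larger sample would not dilute it. The plan collects a reading made away from the patient and then excludes it from the analysis.

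**Working it through.** **Does the masking risk follow from the text?** Treatment current = PT + 0.75 × (MTT − PT), which exceeds PT whenever MTT > PT. PT is where the patient first feels the current. Sham current is zero. The two arms therefore differ in sensation by design. Whether patients act on it is an inference.

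**Inputs for size.** From section 17.2: PAS 1–5 in 50% of controls and 65% of PES patients, and 100 per arm, with at most 360 evaluable in total (180 per arm). From section 17.4: one-sided 0.025. Assumed, because the article does not give them:
- a control split of aspiration/penetration/safe = 50/15/35;
- 1 in 10 PES aspirators rated as penetration.

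**Planned PAS effect, PES 35/15/50 against control 50/15/35**
- Wins: 0.50 × 0.65 + 0.15 × 0.50 = 0.325 + 0.075 = 0.4000
- Losses: 0.35 × 0.50 + 0.15 × 0.35 = 0.175 + 0.0525 = 0.2275
- Net win: 0.1725

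**No true effect, with misrating, PES 45/20/35 against control 50/15/35**
- Wins: 0.35 × 0.65 + 0.20 × 0.50 = 0.2275 + 0.1000 = 0.3275
- Losses: 0.35 × 0.65 + 0.15 × 0.45 = 0.2275 + 0.0675 = 0.2950
- Net win: 0.0325

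Ratio: 0.0325 / 0.1725 = 0.19.

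**Sensitivity to the unknown split.** Let p be the control penetration share. Moving 0.05 of PES patients from aspiration to penetration changes the net win by 0.05 × (0.50 + p). Moving 0.15 from aspiration to safe, as in the planned effect above, changes it by 0.15 × (1 + p).

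| p | Misrating | Planned | Ratio |
|---|---|---|---|
| 0 | 0.0250 | 0.1500 | 17% |
| 0.15 | 0.0325 | 0.1725 | 19% |
| 0.25 | 0.0375 | 0.1875 | 20% |

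**Type I error.** The Finkelstein-Schoenfeld test (PAS category, then DOSS) was simulated under a true null with 4,000 replicates per cell. The assumptions were DOSS SD 1.5, PAS–DOSS correlation 0.5, 80% of PAS 1–5 rated safe (a 50/10/40 split), a fixed sample size and no interim analysis.

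| Share of PES aspirators rated as penetration | 100 per arm | 180 per arm |
|---|---|---|
| 0 | 2.8% | 2.0% |
| 10% | 5.0% | 6.8% |
| 20% | 10.4% | 15.6% |

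The simulation standard error near 5% is √(0.05 × 0.95 / 4,000) = 0.3 points, so the zero row agrees with the nominal 2.5%. A second simulation under the same assumptions gave 5.6% and 6.7% at the 10% share.

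**Site blinding.** Section 3.1 says that the records carry the site number. Section 10.2 says that members score without knowing the site. As written, both hold only if the label is hidden from the members, and neither section says that it is.

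**The case against.** The strongest reply is that the trial does blind its local assessors. Treaters and assessors are separate, the assignment is restricted, the sham procedure mimics the active one, and raters are trained. Bias needs a chain: the patient works out the arm, says so to an assessor 24–60 hours after the last session, and the assessor then shifts a category. The documents give no rate for any link, and a sham patient has no active session to compare with. This stands, and it keeps the point to a risk. It does not remove the risk, because none of those controls deals with what the patient feels.

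It also stands that a central reading is a partial remedy. Bedside DOSS at day 7, the second level, has no central rating. The local operator decides when to stop the boluses (section 10.3), which shapes the video. The article does not say whether the videos carry sound.

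A reader might infer more than the text supports:
- *That PAS is scored open-label, or that masking has failed.* Section 3.1 says the opposite, and no unblinding data exist.
- *That the illustrated misrating equals one third of the planned effect.* Non-aspiration would move from 50% to 55%, which is 5 of the planned 15 points, but only on a dichotomised scale. The endpoint has three PAS categories, and on the win–loss scale the share is about 19%.
- *That the planning rates fix how many pairs PAS decides.* They do not, because section 17.2 gives no safe/penetration split.
- *That the site or visit label reveals the arm.* Both arms contribute screening and follow-up videos at every site.
- *That a sensitivity analysis or a blinding check is missing.* Section 17.4 leaves the analyses to an SAP that is not shown. The point is the choice that section 10.2 states.

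The remark that FEES is not scored in duplicate, although both PAS scores are recorded, can be read as no double rating for the endpoint. It is an editorial matter.

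**Conclusion.** The point holds as a cheap improvement to a stated choice, and no figure in the plan is shown to be wrong. Section 10.2 makes the rating more exposed to patient disclosure the sole PAS for all primary analyses, and confines to training a reading made away from the bedside and blinded to treatment. The size is illustrative: with 1 in 10 PES aspirators misrated, about 19% of the planned PAS-level net win, and a type I error of roughly 5–7% against 2.5%. Both rest on an assumed misrating rate in one direction only and an assumed split; the error rates also rest on assumed DOSS parameters. The conflict over site blinding is real but is a matter of wording.

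**What to change.** 1. Amend section 10.2 so that the committee PAS is the PAS in the primary analysis, with the local PAS used only where the video cannot be read. At minimum, lift the training-only limit and pre-specify the primary Finkelstein-Schoenfeld test with committee PAS as the key sensitivity analysis.
2. Report local–committee agreement on PAS by arm. A difference between arms would be the direct sign of the bias described here.
3. Keep the local PAS for eligibility and care, so that patient management does not change.
4. Reconcile sections 3.1 and 10.2 on whether committee members can see the site number.

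Cost: wording and analysis work, because the committee scores are already in the eCRF. If the committee PAS becomes primary, the rater differs between eligibility and outcome, and unreadable videos bring the local rating back for some patients; their number should be reported by arm. The change does not protect bedside DOSS and does not remove patient expectation effects.

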### FEES stopping criteria

10.3

If gross aspiration (PAS ≥6, see below) of two consecutive bolus trials of the same consistency are observed, that consistency should be stopped and the investigator administering the FEES (or trained and authorized designee) should decide either to move to the next consistency (to assess any potential dietary modification) or terminate the FEES. A ‘Stop’ may be applied at any time if the investigator administering the FEES (or trained and authorized designee) feels it to be unsafe for the patient to continue.

## Assessment scoring scales

11

### Penetration aspiration scale score (incl. definitions):

11.1

The PAS is a validated 8-point ordinal scale that quantifies penetration and aspiration events observed during instrumental swallow assessment.^[38]^ The scale ranges from 1 (normal swallow: material does not enter airway) to 8 (severe aspiration: material enters the airway, passes below the vocal folds & no effort is made to eject). Swallowing severity will be assessed using the PAS observed during FEES at screening and on day 2 (approx. 24–60 hours) after completion of the final PES treatment. The worst PAS score for each thin liquid bolus will be recorded in the eCRF. IFRC PAS scores will be entered in a separate portion of the eCRF.

### Functional oral intake scale (FOIS)

11.2

The FOIS was developed to document the functional level of oral intake of food and liquid in stroke patients with dysphagia.^[39]^ It is a 7-point ordinal scale easily completed by clinicians based on information contained in medical charts, dietary journals, and/or patient reports. Verification of patient reports may be obtained by a spouse or family members or from a variety of sources for institutionalized patients. The score ranges from 1 (nothing by mouth) to 7 (total oral diet with no restriction). FOIS scores will be recorded in the eCRF at the screening, day 2, 7 ± 1 days and 14 ± 1 days visits.

